### 5) *A brief data analysis plan and description of the nature of the variables to be derived*

As noted previously, depression and trauma were the two mental health problems that were prominently identified in the qualitative research (IRB#3047) that preceded this intervention evaluation phase of the project. Depression symptoms will be measured using a modified, locally validated version of the Hopkins Symptoms Checklist (HSCL) and trauma exposure and symptoms will be measured using a modified, locally validated version of the Harvard Trauma Questionnaire (HTQ). The data generated from the validation study has been used to develop depression and trauma scale cutoff scores for the study population. The counselors will calculate the total score for these subscales during the initial screening interview, since scores on either of these scales above the cutoffs are part of the eligibility criteria (13 or above for

depression symptoms and 45 or above for trauma symptoms). Following randomization into a case group and a wait-control group, the counselors will provide the intervention to the case group. At the end of the intervention, the case group and the wait-control group will be re-interviewed using the same instrument employed in the screening interview. The mean change in the various subscales between pre and post intervention interviews will be calculated and subtracted from the mean change (calculated in the same way) for the wait-control group. The differences will be the amount of change on each scale due to the intervention.

In terms of statistical analysis, we will keep the data on study participants in the intervention group who get other standard of care treatment or participants in the wait-control group who need immediate treatment. All study participants who meet screening criteria for eligibility and enroll in the study will be included in the analysis on an intent to treat basis.

6) *If human biospecimens (blood, urine, saliva, etc.) will be collected, provide details about collection, volume (ml) or number, use, storage, identification, and disposal.*

Not Applicable

7) *Describe how subjects will be screened for eligibility and assigned to study/intervention and comparison/control groups.*

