In the case of individuals who evidence signs of active suicidal ideation, counselors and clinical supervisors have been trained on suicide assessment as part of their CBI training. In all cases involving potential danger of a client harming him/herself or others, counselors will follow the study Safety Plan to request assistance in assessing the need of follow-up care and services for that individual. On a case-by-case basis, the study team will work with the counselor and clinical supervisor, along with [name] and the study team's clinical experts, to determine whether to offer the individual the study treatment (if they are excludable from the study intervention), or the study intervention (if they are otherwise eligible and no longer deemed an active risk to harm themselves or others), or some other available and appropriate treatment.

*Randomization process:*

If the subject is deemed eligible and consents to join the trial, the subject will be randomly allocated to the case group to receive treatment immediately or to the wait-control group. The randomization process will be as follows:

1. Each counselor will receive a list of participant ID numbers in sequence (i.e. 1-15) which have been randomly allocated to either intervention or wait-control via a random number generator, with a 1 to 1 ratio of intervention to wait-list. There will be one list for each counselor. Counselors will not be aware how numbers have been allocated.
2. For each counselor, a paper indicating the treatment assignment (intervention or wait-list) will be folded and stapled directly to the back of consent forms that are pre-numbered with a client ID number.
3. Once the subject has consented to be in the study, the counselor will assign a number to the client in the order in which they are recruited. They will remove and unfold the paper attached to the form that corresponds to their ID number, and will inform the subject whether they will begin the intervention immediately or will be put on the wait list.

The study investigators will keep master lists for each counselor which indicate the allocated group status (intervention or wait-control) for each client ID number to ensure fidelity to the randomization model.

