No placebos will be used. There will be a wait-control group who will not initially receive treatment. Instead they will wait until the intervention has been completed for the case group, a period of no more than 3 to 4 months. They will then be reassessed before beginning treatment. The reason for the initial non-treatment is that we do not have evidence of the effectiveness in this setting for the treatment included in the study.

Once wait-control group participants have waited the full intervention period (3 to 4 months), they will then receive the intervention from the counselor they saw at intake (unless it is established that the intervention is shown to be unhelpful or harmful). In addition, controls will be provided the study therapy if their symptoms become clinically significantly worse, or (in severe cases where the person is a risk to themselves or others) they may be referred to other sources of care (either Mae Tao Clinic or Mae Sot Hospital).

*11) Provide a definition of treatment failure or participant removal criteria.*

Clinical treatment failure is defined as an individual completing less than 6 sessions of the Components-Based Intervention. Available research suggests that this is a significant “dose” of therapy to see treatment effects. The success or failure of the intervention failure will not be assessed at the individual level but only at the group level. Failure at the group level for the intervention would consist of less than a 20% difference in change in mean symptom severity score between pre and post intervention assessment compared with the wait-control group.

Participants would be assessed on a case-by-case basis if they were in danger of suicide or doing harm to others. This will be defined by demonstrating actively suicidal or homicidal thoughts. At that point, the counselors will work with their supervisors to seek more specific psychiatric assistance with the individual.

*12) Describe what happens to participants receiving therapy when the study ends or if a subject's participation ends prematurely.*

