## **7. Consent process and documentation:**

- a. *Describe who will obtain informed consent from participants, and how, when and where consent will be obtained.*

Prior to the screening process and intake interview, the counselor will verbally consent participants, informing them of the interview process, the intervention therapy, the re-interview process and the possible risks and benefits of participation. The interview will take place at a private location convenient to the potential client and could include the BBP, AAPP, SAW, or MTC offices or a private home. At the beginning of the consent process, the counselor will establish that the person meets eligibility criteria for inclusions—that is, they are 18 years or older, a Burmese national, and resident in the Mae Sot area. During the oral consent process, the potential client will be informed that they will first be asked a series of screening questions to assess their mental health symptomology. If the person is determined to be eligible for inclusion in the intervention study on the basis of these higher symptom scores, they will be told that they will be randomized into a case group or wait-control group and informed that they will either start the intervention within approximately one week or will be asked to wait several months. Following the intervention, both groups will be re-interviewed.

Thus the screening consent form will offer a recruited individual to consent to be screened for trauma exposure and for depression and trauma symptoms only. If the individual is deemed eligible for inclusion, the study consent form will offer the potential client an opportunity to complete the intake/assessment interview and to be randomized into a case or wait-control group for treatment (for the case group), and a follow-up interview several months later. For those in the wait-control group, they will be further asked if they are willing to be contacted once a month by the counselor while they are waiting for the follow-up interview.

Failure to show up for first session will disenroll a person from the study; we do not regard a client as fully consented unless they show up for Session 1 as they may have changed their mind after discussing participation with family members. If a client clearly (in the view of the counselor, clinical supervisor and study team) does not have mental capacity to give consent, then that person would not be asked to be in the study.

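### Disenrolling Session 1 no-shows filters the randomised arms unequally after allocation is known, so the analysis set is not intent to treat by randomised group

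*Protocol*

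**What the plan says.** Section 4 item 7 (Randomization process) places allocation at consent: "If the subject is deemed eligible and consents to join the trial, the subject will be randomly allocated to the case group" or to the wait list. The counselor then opens the paper attached to the consent form and "will inform the subject whether they will begin the intervention immediately or will be put on the wait list".

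Section 7a describes what follows. Participants are told that "they will either start the intervention within approximately one week or will be asked to wait several months". It then sets the rule at issue: "Failure to show up for first session will disenroll a person from the study". The reason given is that "we do not regard a client as fully consented unless they show up for Session 1", since the person may have reconsidered after talking with family.

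For wait-controls, section 4 item 10 says of the end of the waiting period: "They will then be reassessed before beginning treatment". Section 4 item 1 gives the same order. Item 10 also has an exception: "controls will be provided the study therapy if their symptoms become clinically significantly worse".

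Section 4 item 5 says that participants who meet the screening criteria and enroll "will be included in the analysis on an intent to treat basis". Section 4 item 12 says that the counselor contacts anyone who misses a scheduled session, to learn whether this is a formal withdrawal or a barrier that can be overcome.

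**The concern.** Randomisation makes the arms comparable only if what happens after it does not decide who is counted. Here a person who already knows the assignment can leave the study by not attending an appointment that, on the planned schedule, only one arm has before the outcome is measured. Wait-controls who are equally ambivalent meet no such test: their monthly check-ins (section 4 items 3 and 7) carry no disenrolment rule.

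The primary comparison is at stake. Section 4 item 5 attributes to the intervention the difference between arms in mean change. If the case-arm mean covers attenders while the control-arm mean covers people who were never tested for attendance, that attribution fails. This is also a rule of conduct, not only of analysis. A person treated as disenrolled and not fully consented has no stated route to the follow-up interview, and an analysis plan cannot recover an outcome that was not collected.

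**Working it through.** **1. Order of events**

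| Step | Case arm | Wait-control arm |
|---|---|---|
| Consent, paper opened, arm disclosed (section 4 item 7) | yes | yes |
| Session 1, with disenrolment for a no-show (section 7a) | about one week later | not scheduled |
| Outcome interview (section 4 items 2 and 10) | end of case-arm intervention | same time |
| Session 1 | already past | after the outcome interview |

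If the rule were also applied to controls at their own later Session 1, it would remove people whose outcome is already recorded. That does not restore comparability either.

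**2. Two readings of *enroll* in section 4 item 5**

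- Enrolment happens at consent and allocation. Section 7a then removes people whom item 5 promises to analyse, and the two sections contradict each other.
- Enrolment is complete only at Session 1. The two sections then agree formally, but the analysis set is fixed after the arm is known and by a condition that differs by arm. This reading also sits badly with section 4 item 2, which times the follow-up of both groups from the date of enrollment; for controls that can only be intake.

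Neither reading gives intent to treat by randomised group.

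**3. The plan's own sample size (section 4 item 14)**

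Inputs: effect 0.50 SD, power 0.80, alpha 0.05 (two-sided assumed), design effect 1.5, drop-out 25%. A two-sample t-test needs 64 per arm, and 64 × 1.5 × 1.25 = 120, the stated figure. Planned recruitment is 150 per arm. After drop-out and design effect, 150 × 0.75 / 1.5 = 75 effective per arm, which gives power 0.865 for 0.50 SD.

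**4. Illustration A: no-shows gain nothing**

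The protocol gives no Session 1 no-show rate. Assume a fraction f of 5-15% (7.5 to 22.5 of 150), no benefit in no-shows, no prognostic difference, and that all would otherwise be re-interviewed. Then

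observed effect = ITT effect / (1 − f)

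- f = 0.05: 0.50 / 0.95 = 0.53
- f = 0.10: 0.50 / 0.90 = 0.56
- f = 0.15: 0.50 / 0.85 = 0.59

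If only half of the no-shows would have been re-interviewed, the inflation at f = 0.10 is 0.95 / 0.90 = 1.056 instead of 1 / 0.90 = 1.11. If CBI does nothing, this mechanism creates no effect.

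**5. Illustration B: no-shows differ in prognosis**

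Let no-shows differ from attenders by g SD in the change they would have had anyway. With no true effect, dropping a fraction q of the case arm shifts the contrast by q × g. Both inputs are assumptions.

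- q = 0.05, g = 0.2: 0.01 SD; two-sided type I error 0.050
- q = 0.10, g = 0.5: 0.05 SD; type I error 0.060
- q = 0.20, g = 0.5: 0.10 SD; type I error 0.089
- q = 0.25, g = 0.8: 0.20 SD; type I error 0.205

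Type I error uses a normal approximation with 75 effective controls and 75 × (1 − q) effective cases. The last row is extreme: it equals the protocol's whole 25% withdrawal allowance. The shift favours CBI if no-shows would have improved less than attenders, and goes against it if they would have improved more.

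**6. Power when no-shows are kept**

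If the effect in attenders is 0.50 SD and no-shows gain nothing, the ITT effect is 0.50 × (1 − f), with 75 effective per arm:

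- f = 0.05: 0.475, power 0.83
- f = 0.10: 0.45, power 0.79
- f = 0.15: 0.425, power 0.74

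**The case against.** The best defence has four parts.

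- *Exclusion is not stated.* Section 7a never says that disenrolled people are left out of follow-up or analysis, and section 4 item 5 limits its promise to those who enroll. This is true. But disenrolled and not fully consented both point to exclusion, and nothing says that these people's data are kept. The least that stands is an analysis set that depends on arm or is left in contradiction.
- *Section 4 item 12 may soften the rule.* If missed sessions are followed up, removal need not be automatic. But the two sections then give different rules for the same event. If item 12 does not reach Session 1, nothing softens the rule.
- *Controls are also lost.* They may withdraw or miss the interview, and about 25% withdrawal is expected overall. That is ordinary attrition, which both arms face. The allowance protects power, not comparability.
- *The rule protects consent.* Consent is oral and a change of mind deserves respect. This stands, and is a reason to move the time for reconsideration, not to abolish it.

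Two stronger readings are tempting and are not supported. A reader might infer that only case-arm people can ever be removed. Section 4 item 10 lets worsening controls receive the study therapy early, so some may face a first session before their outcome interview; they are a selected subset and do not balance the filter. A reader might also infer that the bias most likely favours CBI. The protocol does not support this: the outcome is change from baseline, and no-shows who already feel better, or who start high and regress more, would push the other way.

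**Conclusion.** The concern holds as a matter of sequence and needs no assumed figure. Allocation is disclosed at consent, a later attendance test disenrolls people, and on the planned schedule only one arm meets that test before its outcome is measured. The resulting comparison is not intent to treat by randomised group, and section 7a conflicts with section 4 item 12.

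The direction and size of the bias are unknown. The 0.53-0.59 reading of a true 0.50 SD effect rests on assumed no-shows of 5-15% who gain nothing and would all otherwise be re-interviewed; with partial re-interview it is smaller. The prognostic shift of 0.01-0.20 SD rests on assumed rates and gaps and may take either sign; at 10% no-shows and a 0.5 SD gap, the rise in type I error to 0.060 is modest. The point should be settled before enrolment because missing outcomes cannot be recovered afterwards.

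**What to change.** Reconcile section 4 items 5, 7 and 12 with section 7a:

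- Place any time to reconsider after family discussion before the allocation paper is opened, on the same terms for both arms.
- Define everyone whose paper is opened as enrolled, and analyse them in the assigned arm.
- Replace the disenrolment sentence: a Session 1 no-show is followed up as in section 4 item 12 and invited to the follow-up interview unless consent is actually withdrawn.
- Report withdrawals of consent by arm.

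The cost is wording in the protocol and consent script, and a short delay before allocation if time to reconsider is wanted. The effect estimate may be somewhat smaller and power falls: under the assumptions in the working, from 0.865 with no no-shows to 0.83 at 5% and 0.74 at 15%.

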## **8. Risks:**

- a. Describe the risks associated with the study and its procedures, including physical, psychological, emotional, social, legal, or economic risks.*

There is some risk that persons completing the screening and/or intake/assessment forms may be reminded of past traumatic events and become distressed. The CBI therapy includes discussion and recollection of the traumatic exposure with management of the emotional reactions with the counselor. Research and experience in the West suggests that exposure-based therapies are likely to be effective when treating individuals with post-trauma syndromes. There is some risk that such exposure could be harmful if the reactions are not properly managed. However, the emphasis of the training is on correct management, so that the result should be symptomatic relief. We do not expect any social, legal or economic risks. The identity of torture survivors is well known in the community and some belong to a well-known prisoner association. Assessment and treatment will be organized so as not to interfere with employment or other support activities.

- b. Describe steps to be taken to minimize those risks.*

If persons experience distress while completing the screening interview or the intake/assessment form they will be asked to notify the counselor and are free to pause or stop the assessment. If they remain distressed the counselor will provide counseling based on their existing skills and knowledge, and will offer to see the person again in a day or two for further treatment. With regards to CBI, the training emphasizes the management of reactions to exposure, so that the exposure should result in improvement and relief.

For all interventions, during each treatment session the current state of the client's symptoms is assessed. If indicated, the client will be referred by the counselor for assessment by the clinical supervisor, and, if indicated further, be treated by them or referred to a local facility for further assessment and treatment. The clinical supervisors will meet with the counselors weekly to monitor the progress of the program and how things are going with each client. To monitor the individual clients, the counselors will fill out session monitoring forms (see attachments) for each client after each session. As part of these forms, the counselors will record any changes in symptoms and problems that the client has. These forms, together with the weekly supervisory discussions, will form the basis for monitoring the current state of participants' symptoms and will be able to detect if symptoms worsen and the client needs additional services.

The Safety Plan that has been established for the intervention (and modified from a plan that has been used in Iraq) involves the counselor at each weekly session asking the client a series of questions, first explaining what—"I'm going to ask you some questions about safety"—and then why—"We ask every person these questions often because we want to be sure you're safe." The four questions are"

1. "Do you think about killing yourself"
2. "Do you have a plan to kill yourself?"
3. "Do you have a way to carry out this plan?"
4. "Have you ever tried killing yourself?"

If the client responds "yes" to any of the questions, the counselor should call their supervisor immediately after the session. If a client responds "yes" to either of the last 2 questions, the counselor is to call his/her supervisor immediately with the client still in the room. The counselor will ask the client to do their "safety work:" "We want to make sure you are safe. I know this might be hard. Can you give me your word that you will keep yourself safe for a short period of time - just over the next day?" The counselor will then encourage the client to set up a safety watch: "We want to help you keep yourself safe. Many times we use family members or friends to do this. Can you help me think of who in your family or which of your friends can be around? Can we work together to bring these people in to agree to help be with you so that you are safe?" The counselor and clinical supervisor will consult with the safety response team to determine appropriate next steps for care and treatment.

The safety response team on the ground comprises the counselor, the clinical supervisor, [name], MD, (a clinical supervisor, and a member of the study team, and medical advisor to SAW), the organizational supervisor (there is one from each organization including [name] from BBP) and [name] from the Community Consultation Team. The team would consult amongst themselves and also contact [name], JHU Project Director in the field. She would in turn inform the JHU team, including the P.I. and [name] (JHU faculty, a co-investigator and a psychologist) before determining the most appropriate course of action for a client. Options could include having [name] manage the case, asking Mae Tao Clinic (which has a Counseling Center and in-patient services) to manage the case, or referring the case to Mae Sot Hospital. Female clients may also be referred to SAW for temporary residence in one of their shelters and safe houses.

- c. *Describe the research burden for participants, including time, inconvenience, out-of pocket costs, etc.*

For those who participate only in the screening interview, the burden would involve a 20-minute interview. Given that persons recruited for the initial screening interview would be assisted with transportation to the interview site, we do not anticipate that they would incur any out-of-pocket costs. Among those enrolled in the study, for the case group, the burden will be a one-hour initial assessment interview, one hour a week sessions for approximately 10 weeks of CBI therapy (including the time to the counseling site), and a one-hour post-intervention assessment. For the wait-control group, the burden will involve two one-hour assessment interviews and three to four monthly contacts while the intervention is being provided to the case group clients. Given that all of these services are in Mae Sot or nearby communities, the travel time required to get to them are minimal. As noted previously, local transportation costs will be reimbursed for study participants.

- d. *Describe how participant privacy will be protected during data collection if sensitive questions are included in interviews.*

Counselor-subject interactions, including the initial screening and intake interviews and subsequent counseling sessions, will be carried out in private locations, including the BBP, SAW, AAPP, or MTC offices, with preference given to the BBP office which has three private counseling rooms available.

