The Components-Based Intervention includes psycho-education, relaxation, life-enhancing skills (problems solving and safety planning), family support, and cognitive processing of life problems and traumatic events. The CBI model is being tested in a JHU study in Southern Iraq and preliminary results suggest that it may be effective for the population of displaced Burmese in Thailand. The duration of sessions is one hour, the frequency of treatment is weekly, and the recommended number of sessions in the Thailand/Burma border site is 10.

In February-March 2011, US-based clinical psychologists trained 20 counselors and 4 supervisors in CBI techniques. The training curriculum involved 10 full days (8:00am – 4:00pm) of live training including didactic explanations, demonstration role-plays and small-group role-plays. CBI components covered in the training included:

- 1) Pre-Treatment (consent, intake/screening, and assessment)
- 2) Encouraging Participation (why mental health services are important)
- 3) Psychoeducation (information about problems and treatment process)
- 4) Behavioral Coping Skills: Relaxation (helping clients learn ways to cope with stress)
- 5) Behavioral Coping Skills: Behavioral Activation (helping clients to do activities they enjoy)
- 6) Cognitive Coping (counselors talk with clients about how thoughts, feelings and behavior are connected and how to think in different ways in order to change feelings and actions)
- 7) Gradual Exposure (for Trauma) (counselor engages client in a direct detailed discussion about traumatic events he/she has experienced and connected thoughts and feelings)
- 8) Live Exposure (for Fear-based Anxiety) (counselors talk with clients about slowly, step-by-step, facing a place/thing they are afraid of)
- 9) Cognitive Reprocessing (counselors challenge client's unhelpful and inaccurate thoughts)
- 10) Enhancing Safety (counselors ask clients specific questions about safety and suicidal ideation and work with client to develop and implement a safety plan)

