*Training on Consent and Screening Procedures:* We plan to begin the actual intervention study with CBI in June 2011 (corresponding to Month 5 in the table below). Prior to that, JHU study faculty will provide training to all counselors and clinical supervisors on how to carry out consent and screening procedures, including administering the study consent form and interpreting depression and trauma severity scores.

*Screening:* A screening process, and allocation to either an intervention (case) group or temporarily to a wait-control group, will continue until the practicum round of CBI training has been completed in late June or early July. If a sufficient number of clients for the intervention group are not identified by early July, screening and enrollment could continue beyond that time.

*Service Provision:* Beginning in late June or early July 2011, the intervention will begin with weekly sessions provided by the counselors to the client and with supervision provided in the form of weekly meetings between the counselor and clinical supervisor and in the form of weekly phone conversations between the clinical supervisors and the JHU trainers/clinical psychologists. Both intervention and control clients will be monitored using separate client monitoring forms. These forms will include information on the clients' well-being, any treatment or medication they are receiving, and whether or not the client's are in danger to themselves or others. Clients who are in danger of committing suicide will be discussed immediately with supervisors, or referred if supervisors are not immediately available. There is a Safety Plan (see attachment) in place for this project that includes a response team of the following: the counselor, the counselor's clinical supervisor, a medical doctor who is part of the project team, and the Field Project Coordinator. The Project Director will provide support for this response team at all times and will be in regular contact with the Project PI. A copy of the Safety Plan protocol is included in the IRB application.

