At the end of the study those counselors providing interventions found to be effective will continue to provide treatment, both to those currently receiving the treatment and to new clients. Persons who have not yet received the new intervention will be eligible to receive it regardless of whether they had previously received any treatments. If a subject's participation ends prematurely for whatever reason, they could continue to work with a clinician or other care services as needed.

Any participant who does not come to a regularly scheduled session will be followed up by the counselor to determine whether they are a formal withdrawal or if there is some other barrier that can be overcome to continue treatment. If the participant does not want to participate further, the counselor or project staff will try to find out the reason for withdrawal. Otherwise, no further action will be taken. Our sample size calculations are based on an assumption that about 25% of participants will choose to withdraw from the study and from treatment.

*13) Describe the process for referring subjects to care outside the study, if needed.*

One local counterpart, Mae Tao Clinic, operates a primary care clinic with a Counseling Center and with referrals to Mae Sot Hospital, a Thai hospital in Mae Sot with limited in-patient psychiatric services. Clinical supervisors for the CBI intervention will be in weekly contact with JHU and consulting CBI experts on a routine basis and will communicate with them on an as needed basis. Persons who are found at screening or during the study to be in active danger of harming themselves or others will be immediately discussed with clinical supervisors and the safety response team for referral to the nearest and most appropriate treatment site.

*14) For studies that evaluate interventions, have a randomized study design, and/or are a clinical trial, provide power calculations for projected sample size.*

To calculate sample size, we relied on a pair-wise comparison – that is comparing the intervention to the wait-control condition. We calculated sample size and power calculations using effect size analyses of depression and trauma symptom scores. We estimated that to find a moderate effect size (.50) for either depression or trauma, we would need 120 participants in each arm. We used power=0.80, alpha=0.05, a design effect of 1.5, a drop-out rate of 25%, and a 1:1 ratio of intervention (case) to wait-control.

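### A client who reports a current suicide plan, but denies means and any past attempt, need not be discussed with a supervisor until after the session

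*Protocol*

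**What the plan says.** Section 8(b) of the protocol (Risks, steps to minimize them) summarizes the Safety Plan. The counselor asks four questions at every weekly session:

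1. thoughts: "Do you think about killing yourself";
2. plan: "Do you have a plan to kill yourself";
3. whether the client has a way to carry out that plan;
4. whether the client has ever made an attempt.

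Two call rules follow. After a yes to any question, "the counselor should call their supervisor immediately after the session". After a yes to question 3 or question 4, "the counselor is to call his/her supervisor immediately with the client still in the room". The section then describes a promise to stay safe over the next day, a watch by family or friends, and consultation with a safety response team.

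Three statements in section 4 bear on these rules:

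- Item 7 makes the Safety Plan the operating instruction: "In all cases involving potential danger of a client harming him/herself or others, counselors will follow the study Safety Plan to request assistance".
- Item 2 (Service Provision) says: "Clients who are in danger of committing suicide will be discussed immediately with supervisors, or referred if supervisors are not immediately available".
- Item 13 says that anyone judged, whether at entry or later, "to be in active danger of harming themselves or others will be immediately discussed with clinical supervisors and the safety response team".

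Item 11 of section 4 defines danger by the presence of actively suicidal or homicidal thoughts. It does not mention a plan or means.

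**The concern.** Question 2 is not one of the two questions that trigger the in-room call. A counselor who follows section 8(b) as written can let a client who has just disclosed a current plan go home before any supervisor has heard of it. If the supervisor then wants the client assessed, or referred to the clinic or hospital, the client must first be found again.

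The ordering is also hard to explain from the protocol itself. A past attempt at any time, with present thoughts, plan and means all denied, brings an in-room call. A plan reported today, with means and past attempts denied, does not.

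The rule carries weight because section 11 provides no data and safety monitoring board and relies on monitoring each client individually. The point concerns participant safety only. It does not touch the estimate of treatment effect.

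**Working it through.** The protocol gives no figure to reproduce here. The check applies the two call rules in section 8(b) to every possible set of answers.

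**Inputs.** Four yes/no questions (section 8(b)) give 2^4 = 16 patterns. Sessions are weekly and last one hour (section 2: "The duration of sessions is one hour").

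**Current rule**

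- In-room call, if question 3 or question 4 is yes: 16 − 4 = 12 patterns.
- Call after the session, if questions 3 and 4 are both no and question 1 or question 2 is yes: 3 patterns (question 1 only, question 2 only, questions 1 and 2).
- No call, if all four are no: 1 pattern.
- Check: 12 + 3 + 1 = 16.

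**Patterns that include a plan.** With question 2 = yes there are 2^3 = 8 patterns. Of these, 6 give an in-room call and 2 are deferred: (yes, yes, no, no) and (no, yes, no, no).

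**Rule with question 2 added to the in-room trigger**

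- In-room call, if question 2, 3 or 4 is yes: 16 − 2 = 14 patterns.
- Call after the session: 1 pattern (question 1 only).
- No call: 1 pattern.

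| Tier | Current | Revised |
|---|---|---|
| In-room call | 12 | 14 |
| Call after session | 3 | 1 |
| No call | 1 | 1 |
| Plan reported, call deferred | 2 of 8 | 0 of 8 |

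Two patterns move up (14 − 12 = 2) and none moves down.

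**Coherent answers only.** Some of the 16 patterns are implausible, since means presuppose a plan and a plan presupposes thoughts. Under that restriction, questions 1 to 3 can take 4 forms (none; thoughts; thoughts and plan; all three), and with question 4 there are 4 × 2 = 8 patterns. The current rule gives 4 in-room from question 4 plus 1 from question 3 alone = 5, with 2 after the session and 1 with no call. Of the 4 patterns with a plan, 1 is deferred: thoughts and plan, with means and past attempts denied. The revised rule gives 6, 1 and 1, with 0 of 4 deferred.

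**Size of the delay.** It is at most the remainder of a 60-minute session. The protocol does not say when in the hour the questions are asked.

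**Side by side with section 4.** Item 11 defines danger by actively suicidal thoughts, and item 2 requires immediate discussion of clients in danger. A reported current plan fits item 11 on a natural reading, so item 2 would ask for immediate discussion where section 8(b) allows it to wait. Applying item 11 to a plan is an inference, however. No sentence says that a plan without means counts as danger, and section 8(b) does not forbid an earlier call. This is a tension between sections, not a proven contradiction.

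**The case against.** The strongest reply has four parts.

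- **Clinical judgement.** Where to set the threshold between a plan and the means to carry it out is a triage decision, and this plan was adapted from one already used in Iraq. That is true, but the protocol gives no reason for ranking a past attempt above a current plan.
- **Unseen attachment.** Section 8(b) only summarizes the Safety Plan, and the attachment may already require the in-room call. This stands as a limit on the finding, and the fix allows for it.
- **Existing protection.** Counselors are trained in suicide assessment. The safety promise and safety watch are not limited to questions 3 and 4. Counselors hold contact details (section 5(c)), and sections 4(2) and 4(11) set a broader duty, so section 8(b) can be read as a minimum. These points lower the risk. None of them requires a supervisor to be consulted while the client is present.
- **Short delay and unknown frequency.** The call comes straight after the session, nothing stops the counselor asking the client to wait, and the pattern counts say nothing about numbers of clients. All of this is correct. The concern is the client's possible departure more than the minutes lost, and the number of extra in-room calls under a revised rule cannot be predicted from the protocol.

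**Conclusion.** The concern holds. As written, section 8(b) lets the supervisor call wait until after the session for a client with a current plan who denies means and any past attempt. That is 2 of the 8 answer patterns with a plan, or 1 of 4 if only coherent answers are counted.

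The conclusion rests on section 8(b) reflecting what counselors are actually told to do. It also rests on the view that a current plan deserves at least the urgency given to a past attempt, which the clinical team should confirm. No prevalence is assumed. Nothing is claimed against leaving thoughts alone in the after-session tier, or against the lifetime wording of question 4. The gap is narrow and partly mitigated, but it lies in a suicide-safety rule and is cheap to close, so the change should be made.

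**What to change.** In section 8(b), extend the in-room trigger from the last two questions to the last three, so that a yes to question 2 also leads to a supervisor call while the client is present. Leave question 1 alone in the after-session tier. Keep question 4 and its trigger, the safety promise and safety watch, and the referral route in section 4(2) when no supervisor is available. Make the same change in the attached Safety Plan; if the attachment already requires an in-room call for a plan, bring section 8(b) into line with it.

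The cost is one number in the protocol, the matching edit in the Safety Plan, and a short note to counselors. Extra in-room calls arise only for clients with a plan who deny means and any past attempt. No added staff, visits or form items are needed, and sample size and analysis do not change.
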